# Safety and efficacy of ketorolac in improving the prognosis of acute type A aortic dissection patients: a protocol of a randomized, double-blinded, and placebo-controlled study

**DOI:** 10.1186/s13063-024-08093-x

**Published:** 2024-04-10

**Keywords:** Ketorolac, Stanford type A aortic dissection, Prognosis

## Abstract

**Background:**

Acute type A aortic dissection (aTAAD) is a critical and life-threatening condition. Previous research has demonstrated that the use of ketorolac not only reduces the progression, incidence, and severity of aortic aneurysms in animal models, but also decreases postoperative mortality and complications in patients undergoing open abdominal aortic aneurysm replacement. However, there is a lack of studies investigating the efficacy of ketorolac in treating aTAAD in humans. Therefore, we conducted a study to evaluate the safety and efficacy of ketorolac in patients with aTAAD. Our hypothesis was that ketorolac treatment for aTAAD patients would meet safety indicators and effectively improve patient prognosis.

**Methods/design:**

This study is a single-center, randomized, double-blinded, and placebo-controlled study. A total of 120 patients with aTAAD will be recruited and will be randomized into the ketorolac group and placebo group with a ratio of 1:1. Ketorolac tromethamine 60 mg per 2 ml will be intramuscularly injected within 2 h before surgery, followed by intramuscular injections of 30 mg per 1 ml BID. on the first and second postoperative days in the Ketorolac group, while 0.9% saline will be administered at the same dose, dosage form, and time in the placebo group. This study aims to evaluate the safety and efficacy of ketorolac in improving the prognosis of aTAAD. The primary endpoint is the composite endpoint event concerning drug-related adverse events. Secondary endpoints include drug-related adverse events, laboratory examination of blood, diagnostic imaging tests, clinical biomarkers, etc.

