### Outcomes {12}

#### Primary endpoint

Efficacy: death, organ malperfusion syndrome, permanent dialysis, tracheotomy, neurological impairment, postoperative mechanical circulatory support, and unplanned cardiac reoperation.

Safety: gastrointestinal ulceration, gastrointestinal bleeding, gastrointestinal perforation, postoperative hemorrhage (postoperative hemorrhage exceeding 1000 ml within 24 h), renal failure, liver failure, drug allergies, and other severe adverse events following drug administration.

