### Sample size {14}

The required sample size was calculated using the PASS (15.0.5) software. The primary endpoint of efficacy was used to calculate the sample size. In the literature, the total death rate of hospitalization after surgery was 25% [7], the incidence of organ malperfusion syndrome was 15–33% [19, 20], permanent dialysis was 2.6% [21], tracheotomy was 8% [22], neurological impairment was 6.9% [22], postoperative mechanical circulatory support was 20% [23], unplanned cardiac reoperation was 4.2% [24], and postoperative cardiac arrest was 0.7–5.2% [25]. Therefore, we assumed that the incidence of composite endpoint events in the control group is 70%, and the incidence of composite endpoint events in the ketorolac group is reduced to 40%. Using PASS (15.0.5) software, when the sample size of the ketorolac group and the control group is 53 cases, this difference can be detected with over 90% confidence. Considering that the loss of follow-up rate is higher than 10%, the final total sample size of this experiment is 120 cases, with 60 cases in the experimental group and 60 cases in the control group.

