## Statistical methods

### Statistical methods for primary and secondary outcomes {20a}

Statistical analysis will be performed using SPSS software (version 26.0) and R (× 64 3.5.0). Continuous variables will be presented as mean ± standard deviation. The Kolmogorov–Smirnov test will assess normal distribution. If variables exhibit normal distribution, an independent sample *t*-test will be employed; otherwise, the Mann–Whitney *U* test will be utilized. Categorical variables’ frequency will be expressed as percentages and analyzed using the chi-square test or Fisher’s exact test. It should be noted that we are not conducting an Intention to Treat analysis due to the exclusion of patients with more than 10% missing data. Double-tailed *p*-values and 95% confidence intervals will be reported, with statistical significance defined as *p* < 0.05.

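### The primary endpoint is stated in conflicting ways: an adverse-event composite in the abstract, unranked efficacy and safety lists under Outcomes, and an efficacy composite in the sample size

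*Protocol article*

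**What the plan says.** The protocol article identifies the primary endpoint in three places.

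- **Abstract, Methods/design.** "The primary endpoint is the composite endpoint event concerning drug-related adverse events". The next sentence places the same item among the secondary endpoints: "Secondary endpoints include drug-related adverse events, laboratory examination of blood". No efficacy composite is mentioned as primary.
- **Outcomes {12}, Primary endpoint.** Two lists stand under one heading. One reads "Efficacy: death, organ malperfusion syndrome, permanent dialysis, tracheotomy, neurological impairment, postoperative mechanical circulatory support, and unplanned cardiac reoperation". The other begins "Safety: gastrointestinal ulceration, gastrointestinal bleeding, gastrointestinal perforation, postoperative hemorrhage" and goes on to renal failure, liver failure, drug allergies and other severe adverse events. The section does not say whether these form one composite, two alternatives, or two endpoints that must both succeed.
- **Sample size {14}.** "The primary endpoint of efficacy was used to calculate the sample size". The assumption is that "the incidence of composite endpoint events in the control group is 70"%, falling to 40% on ketorolac. The literature rates behind it include "postoperative cardiac arrest was 0.7–5.2"%, although cardiac arrest is not in the efficacy list under Outcomes.

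Three other sections bear on the point. Trial design {8} calls the study a superiority test without naming an endpoint. Statistical methods {20a} has "statistical significance defined as *p* < 0.05", two-sided, also without naming an endpoint. Safety assessment lists death, malperfusion, tracheotomy, neurological impairment, mechanical circulatory support and cardiac arrest as safety variables. The first five of these are efficacy components under Outcomes.

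**The concern.** A reader cannot tell from the article which result decides the trial. The abstract points to a composite that was not powered, the Outcomes section points to two, and the sample size rests on one of them. The component list of the powered composite also differs between two sections.

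The power statement covers only one of the candidate primary endpoints. If the other one governs, the planned size has no stated justification. Fixing the deciding endpoint after comparative data have been seen would also be hard to defend. Timing is therefore tight: an interim analysis is planned at 60 patients, and Trial status reports 55 already included on 20 March 2024.

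**Working it through.** **1. Reproduce the plan's own figure.** Inputs from Sample size {14} are 70% and 40%, power above 90%, and 53 per arm. The two-sided 0.05 comes from Statistical methods {20a}.

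- Unpooled two-proportion Z test: n = (1.960 + 1.2816)² × (0.7×0.3 + 0.4×0.6) / 0.3² = 10.507 × 0.45 / 0.09 = 52.54, so 53 per arm.
- Power at 53: SE = √(0.45/53) = 0.0921. Then 0.3/0.0921 = 3.256, and Φ(3.256 − 1.960) = 90.2%.
- With the pooled variance under the null, power at 53 is 88.5% and 56 per arm are needed for 90%.
- Loss to follow-up: 53/(1 − 0.10) = 58.9, so 59. The planned 60 per arm allows 1 − 53/60 = 11.7% loss.

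The figure therefore stands, and it stands for the efficacy composite.

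**2. If the abstract's composite is primary.** The document gives no event rates or effect for it, so its power cannot be derived. The following rates are assumptions for illustration only. The test is the pooled Z test at two-sided 0.05 with 60 per arm: power = Φ[(|p1 − p2| − 1.96·SE0)/SE1].

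| Assumed rates | SE0 (pooled) | SE1 (unpooled) | Argument of Φ | Power |
|---|---|---|---|---|
| 20% vs 10% | 0.0652 | 0.0645 | −0.430 | 33% |
| 10% vs 5% | 0.0481 | 0.0479 | −0.924 | 18% |

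At 53 evaluable per arm, halving a higher assumed control rate of 20%, 30% or 40% has power 30%, 46% or 62%.

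**3. If the two lists are separate primary endpoints.** The error rate depends on the decision rule, which the article does not state.

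- *Either alone suffices, each at two-sided 0.05.* The chance of at least one significant result in either direction is 1 − 0.95² = 9.75% under independence, and at most 0.05 + 0.05 = 10% under any dependence. Counting only results in ketorolac's favour (2.5% per test), it is 1 − 0.975² = 4.94% under independence.
- *Both required.* The type I error is not inflated. If the superiority test applies to both lists, superiority would then also have to be shown on the safety list, for which no rates are given.
- *Either suffices, with 0.05 split equally.* At 0.025, the pooled test on 70% versus 40% has 81.7% power at 53 per arm and 86.7% at 60, and needs 66 evaluable per arm for 90%.

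**4. Component list.** Outcomes {12} has seven efficacy components. Sample size {14} cites rates for those seven plus cardiac arrest. The rate for death is a postoperative in-hospital rate, while follow-up runs to 90 days.

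**The case against.** The strongest reply is that the Sample size section settles the matter, because it ties the calculation to efficacy and the figure reproduces. That part stands: the trial does have a powered endpoint, and a reader who inferred that the power attaches to nothing would be wrong. It shows which list was powered, though, and not which list decides the trial. The abstract names the other one, and the body calls both primary.

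A second reply is that decision rules and alpha allocation may sit in an analysis plan that is not shown. That also stands, so the absence of an alpha split is not the point here. Which endpoint is primary is not left to another document, because the article states it in three places that disagree.

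Two stronger readings are tempting.

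- *Success could be claimed on whichever composite is significant, so the error rate nearly doubles to 9.75%.* The document does not say this. The hypothesis in the abstract's Background joins meeting safety indicators with improving prognosis, which suggests both are required. The 9.75% is also conditional on independence and counts results in both directions. As a rate of false success for ketorolac it would be about 4.9%.
- *A superiority test on the safety list would be one nobody could intend.* Background and rationale {6a} cites clinical research suggesting that ketorolac may reduce renal complications, and renal failure is on the safety list. Trial design {8} does not attach superiority to that list either.

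**Conclusion.** The contradiction is real and should be resolved. The abstract, the Outcomes section and the Sample size section do not agree on the primary endpoint, and the last two do not agree on the components of the efficacy composite.

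The power of about 90% (90.2% unpooled, 88.5% pooled, at 53 per arm for 70% versus 40%) belongs to the efficacy composite only. If the abstract governs, the primary endpoint has no sample-size basis. The 33% and 18% illustrate what that could mean, but they rest on assumed rates. Any inflation of the error rate is conditional on an either-suffices rule that the article does not state.

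**What to change.** Before the interim analysis at 60 patients:

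1. Name the powered efficacy composite as the sole primary endpoint in the abstract, Outcomes {12} and Sample size {14}, tested at two-sided 0.05.
2. Use one identical component list in all three places, with postoperative cardiac arrest explicitly in or out.
3. State one time window for the composite and confirm that the 70% control rate matches it, since the cited death rate is in-hospital.
4. Relabel the safety composite as a key safety outcome, reported as a risk difference with a 95% confidence interval.
5. Remove the adverse-event composite as the primary endpoint in the abstract, and check that the registry entry agrees.

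Keeping both lists as primary with a stated decision rule would also remove the contradiction. An equal alpha split would then cost power on efficacy (81.7% at 53 per arm), and requiring both would need a sample-size basis for the safety list.

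Cost: a protocol amendment. Because a listed primary endpoint changes status during recruitment, it may count as substantial under the section on protocol amendments {25}, with notification of the ethics committee and the competent authority. Sample size and data collection need no change on this account.

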**Discussion:**

This study has been approved by the Medical Ethics Committee of Affiliated Nanjing Drum Tower Hospital, Nanjing University Medical College (approval number: 2023–197-02). This study is designed to evaluate the safety and efficacy of ketorolac in patients with aTAAD. All participating patients will sign an informed consent form, and the trial results will be published in international peer-reviewed journals.

**Trial registration:**

The Chinese Clinical Trial Registry (http://www.chictr.org.cn) ChiCTR2300074394. Registered on 4 October 2023.

## Administrative information

Note: the numbers in curly brackets in this protocol refer to SPIRIT checklist item numbers. The order of the items has been modified to group similar items (see http://www.equator-network.org/reporting-guidelines/spirit-2013-statement-defining-standard-protocol-items-for-clinical-trials/).

## Introduction

### Background and rationale {6a}

Acute type A aortic dissection (aTAAD) is considered the most perilous form of aortic disease [1]. Common causes include hypertension, medial degeneration (cystic medial necrosis), and Marfan syndrome [2]. Currently, rapid surgical reconstruction remains the primary treatment option for aTAAD [3–6]. Based on reported references, the in-hospital mortality rate after surgery stands at 25% [7]. Consequently, there is a pressing need to investigate alternative approaches that can effectively decrease surgical mortality.

Previous studies have shown that activated macrophages in mice secrete inflammatory factors, which can enhance migration and invasion capabilities, accelerate degradation of the aortic media, and contribute to the development of type A aortic dissection (TAAD) [8–10]. Additionally, Rho GTPase, an important regulator of cytoskeleton actin and intracellular signal transduction, has been found to be activated in TAAD [11, 12]. In the literature, it has been observed that ketorolac, a nonsteroidal anti-inflammatory drug and inhibitor of the Rho GTPase signaling pathway, can reduce the progression, incidence, and severity of aortic disease in animal models [13, 14].

Previous clinical research has suggested that ketorolac may reduce postoperative mortality, neurological complications, renal complications, and respiratory failure in patients undergoing open abdominal aortic aneurysm replacement surgery [15]. However, it is important to note that this study was retrospective and focused specifically on abdominal aortic aneurysm. Additionally, the 2022 American Heart Association (AHA) guidelines have reported controversy regarding the use of ketorolac in the analgesic treatment of aTAAD [16]. Therefore, our plan is to conduct a single-center, randomized, double-blinded, and placebo-controlled trial to investigate the safety and efficacy of ketorolac in improving the prognosis of aTAAD patients.

### Objectives {7}

The objective of this study is to assess the safety and efficacy of ketorolac in improving the prognosis of aTAAD.

### Trial design {8}

This study adopts a single-center, parallel-group design, employing randomization, double-blinding, and a placebo-controlled approach. It is a superiority test. Patients diagnosed with aTAAD will be actively recruited and subsequently randomized into either the ketorolac group or the placebo group, maintaining a 1:1 ratio. The study encompasses a follow-up period of 90 days.

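### The protocol wants a conclusion on safety, but its only stated framework is a superiority test at p < 0.05, which cannot support one unless ketorolac significantly reduces these harms

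*Protocol article*

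**What the plan says.** - **Hypothesis** (Abstract, Background): two parts, namely that "ketorolac treatment for aTAAD patients would meet safety indicators and effectively improve patient prognosis". Objectives {7} names safety and efficacy together.
- **Primary endpoint** (Outcomes {12}): an efficacy list and, beside it, a safety list that begins "Safety: gastrointestinal ulceration, gastrointestinal bleeding, gastrointestinal perforation, postoperative hemorrhage (postoperative hemorrhage exceeding 1000 ml within 24 h), renal failure, liver failure" and goes on to drug allergies and other severe adverse events. The Abstract describes the primary endpoint in safety terms: "The primary endpoint is the composite endpoint event concerning drug-related adverse events".
- **Framework** (Trial design {8}): "It is a superiority test", with no endpoint named.
- **Test** (Statistical methods {20a}): categorical variables are "analyzed using the chi-square test or Fisher’s exact test", two-tailed at p < 0.05. The same section promises 95% confidence intervals but does not say how they will be used.
- **Sample size {14}**: "The primary endpoint of efficacy was used to calculate the sample size". The assumed rates are 70% v 40%, giving 53 per arm, raised to 60 for losses. No rate is given for the safety composite.
- **Intended reading** (Discussion): if the hypothesis is borne out, ketorolac may be regarded as safe.

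**The concern.** Safety is a claim that there is no unacceptable excess of harm. A superiority test addresses a different question, whether the arms differ. For the primary safety list, a favourable superiority result would mean significantly fewer gastrointestinal, bleeding, renal and hepatic events on ketorolac than on saline. The protocol's own Safety assessment section names gastrointestinal reactions, gastric bleeding and possible liver and kidney damage as the drug's main adverse reactions, so such a result is not the one to plan for. The likelier results are a significant excess or no significant difference, and the second is not evidence of safety.

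At stake is the first half of the trial's question. The Discussion reports that guidelines advise caution with this drug in acute aortic syndrome, and the monitoring section calls the study high-risk. A conclusion of safety that the analysis cannot bear could mislead practice.

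**Working it through.** **1. The plan's own figure.** Inputs from Sample size {14}: 70% v 40%, over 90% power (the text says confidence); two-sided 0.05 from {20a}.

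n = (1.960 + 1.282)² × (0.70×0.30 + 0.40×0.60) / 0.30² = 10.51 × 0.45 / 0.09 = 52.5, so 53 per arm.

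This matches. 53/60 leaves room for 11.7% loss, which agrees with 60 per arm. The trial is therefore sized for a 30-point difference in efficacy, and nothing in the calculation concerns safety.

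**2. What the same test does with an excess of harm.** The protocol gives no safety rates, so those below are assumptions, shown as a range. Worked case, 10% v 20% at 60 per arm, with pooled variance under the null:

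- mean rate 0.15; null SE = √(2×0.15×0.85/60) = 0.0652; 1.96 × 0.0652 = 0.1278
- SE under the alternative = √((0.09 + 0.16)/60) = 0.0645
- power = Φ((0.10 − 0.1278)/0.0645) = Φ(−0.43) = 33%, so about 67% of trials are non-significant.

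Exact binomial enumeration of the uncorrected chi-square test gives these probabilities of p ≥ 0.05:

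| Assumed rates (placebo v ketorolac) | 60 per arm | 53 per arm |
|---|---|---|
| 5% v 10% | 83% | 85% |
| 10% v 20% | 67% | 70% |
| 15% v 30% | 49% | 53% |
| 20% v 40% | 32% | 37% |
| 30% v 60% | 8% | 12% |
| 20% v 30% | 75% | 77% |
| 30% v 40% | 79% | 80% |

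Fisher's test is more conservative: for 10% v 20% it gives 75% at 60 per arm and 79% at 53.

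The result for a doubling depends heavily on the baseline. The result for a fixed 10-point excess does not: at 60 per arm it is non-significant in about 67–79% of trials across baselines of 10–30%. Detecting 10% v 20% with 80% power would take 199 per arm.

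**3. What the promised intervals could show.** With equal observed rates p, the 95% half-width is 1.96 × √(2p(1−p)/60):

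- p = 10%: 1.96 × √(0.18/60) = 10.7 points
- p = 20%: 1.96 × √(0.32/60) = 14.3 points
- p = 30%: 1.96 × √(0.42/60) = 16.4 points

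So even identical observed rates would leave an excess of about 11 to 16 points not excluded. At 53 per arm the range is 11.4 to 17.4 points.

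**4. Whether a criterion is stated.** Trial design {8}, Outcomes {12}, Safety assessment, Sample size {14}, Statistical methods {20a} and Interim analyses {21b} contain no margin, no acceptable rate of harm and no bound on excess harm. The only stated rule is p < 0.05 for a difference.

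**The case against.** The sentence in Trial design {8} describes the trial as a whole and does not mention safety. Since Sample size {14} is tied expressly to efficacy, the ordinary reading may be superiority for efficacy alone. A reader might infer that the plan will declare ketorolac safe whenever p ≥ 0.05. No section says so, and the Discussion's remark on safety states no decision rule. That objection stands.

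Nor is it right that a safety conclusion could rest only on a non-significant result. A significant reduction in harm would support it. Confidence intervals are already promised. Adverse events will be graded and their incidence calculated, and a DSMB will oversee safety and effectiveness data. Five items in the Safety assessment section (death, organ malperfusion, tracheotomy, neurological impairment, mechanical circulatory support) also belong to the efficacy composite, so a benefit there would bear on part of the safety assessment. This too stands, but it does not reach the gastrointestinal, bleeding, renal and hepatic events that form most of the primary safety list.

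The last objection is that a safety margin may sit in a full protocol, analysis plan or DSMB plan that is not shown. The absence of a margin from a journal article would not by itself be a finding. The point here is what the article does state: safety as a primary question, one unqualified superiority framework, one difference rule, and an expected conclusion of safety. A margin held elsewhere would still have to be reconciled with that text.

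**Conclusion.** The point holds in this form: the stated framework does not fit the stated safety question. Unless ketorolac significantly reduces these harms, the superiority test cannot support a conclusion of safety, and the promised intervals have no criterion attached.

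The size depends on safety rates that the protocol does not give. With 60 per arm, a doubling would be non-significant in about 83% of trials at 5% v 10%, falling to 32% at 20% v 40% and 8% at 30% v 60%. It would therefore be wrong to say that this trial misses a doubling two times in three as a general property; that figure belongs to the assumed 10% v 20%. The finding for a 10-point excess (about 67–79%) is steadier over the baselines tried.

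This should be fixed, but it is not disabling: the efficacy test and the sample size are untouched, and low power for harms is usual in a trial sized on efficacy.

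**What to change.** - In Trial design {8} and Statistical methods {20a}, say that superiority applies to the efficacy composite.
- For the primary safety composite, report the risk difference with its two-sided 95% confidence interval, state the largest excess harm that the interval does not exclude, and say that p ≥ 0.05 will not be read as showing safety.
- If the trial is to claim that the safety indicators are met, require the upper confidence limit to lie below a margin that the sponsor and the DSMB fix before outcome data by arm are seen. Timing matters: Trial status reports 55 patients included by 20 March 2024, and an interim analysis is planned at 60.
- Align the Discussion's statement about safety with this rule.

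**Cost:** wording only, with no added patients and no change to treatment. The downside is that with 53–60 per arm the trial will probably have to report that a sizeable excess harm is not ruled out. As an illustration, if the true rate were 10% in both arms, the chance of meeting a 10-point margin at 60 per arm would be about Φ(0.10/0.0548 − 1.96) = Φ(−0.13) = 45%, and of meeting a 15-point margin about Φ(0.15/0.0548 − 1.96) = Φ(0.78) = 78%. These margins only show what the sample can resolve; they are not recommendations.
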